# Minimally invasive versus open pancreatoduodenectomy for pancreatic and peri-ampullary neoplasm (DIPLOMA-2): study protocol for an international multicenter patient-blinded randomized controlled trial

**DOI:** 10.1186/s13063-023-07657-7

**Published:** 2023-10-12

**Keywords:** Minimally invasive, Laparoscopic, Robot-assisted, Pancreatoduodenectomy, Whipple, Pancreatic surgery, Pancreatic cancer, Peri-ampullary cancer, Pancreatic ductal adenocarcinoma

## Abstract

**Background:**

Minimally invasive pancreatoduodenectomy (MIPD) aims to reduce the negative impact of surgery as compared to open pancreatoduodenectomy (OPD) and is increasingly becoming part of clinical practice for selected patients worldwide. However, the safety of MIPD remains a topic of debate and the potential shorter time to functional recovery needs to be confirmed. To guide safe implementation of MIPD, large-scale international randomized trials comparing MIPD and OPD in experienced high-volume centers are needed. We hypothesize that MIPD is non-inferior in terms of overall complications, but superior regarding time to functional recovery, as compared to OPD.

**Methods/design:**

The DIPLOMA-2 trial is an international randomized controlled, patient-blinded, non-inferiority trial performed in 14 high-volume pancreatic centers in Europe with a minimum annual volume of 30 MIPD and 30 OPD. A total of 288 patients with an indication for elective pancreatoduodenectomy for pre-malignant and malignant disease, eligible for both open and minimally invasive approach, are randomly allocated for MIPD or OPD in a 2:1 ratio. Centers perform either laparoscopic or robot-assisted MIPD based on their surgical expertise. The primary outcome is the Comprehensive Complication Index (CCI®), measuring all complications graded according to the Clavien-Dindo classification up to 90 days after surgery. The sample size is calculated with the following assumptions: 2.5% one-sided significance level (α), 80% power (1-β), expected difference of the mean CCI® score of 0 points between MIPD and OPD, and a non-inferiority margin of 7.5 points. The main secondary outcome is time to functional recovery, which will be analyzed for superiority. Other secondary outcomes include post-operative 90-day Fitbit™ measured activity, operative outcomes (e.g., blood loss, operative time, conversion to open surgery, surgeon-reported outcomes), oncological findings in case of malignancy (e.g., R0-resection rate, time to adjuvant treatment, survival), postoperative outcomes (e.g., clinically relevant complications), healthcare resource utilization (length of stay, readmissions, intensive care stay), quality of life, and costs. Postoperative follow-up is up to 36 months.

**Discussion:**

The DIPLOMA-2 trial aims to establish the safety of MIPD as the new standard of care for this selected patient population undergoing pancreatoduodenectomy in high-volume centers, ultimately aiming for superior patient recovery.

**Trial registration:**

ISRCTN27483786. Registered on August 2, 2023

## Background

Pancreatoduodenectomy (PD) is a major and complex surgical procedure used to treat various pathologies affecting the pancreatic head, duodenum, ampulla, and distal bile duct and is characterized by a high technical difficulty and challenging postoperative management. Although major improvements in the past decade, such as sub-specialization, centralization, and enhanced recovery protocols, have decreased perioperative mortality, PD remains associated with significant perioperative morbidity which strongly impacts patients’ quality of life as well as healthcare resources. Therefore, much could be gained by optimization of perioperative care and surgical techniques (Fig. 1).

**Fig. 1 Fig1:**
[figure not shown]
DIPLOMA-2 study flow chart according to SPIRIT

Over the past two decades, many surgical procedures have shifted from the traditional open surgery approach to minimally invasive surgery to reduce surgical trauma, aiming for less postoperative pain, enhanced postoperative recovery, and thereby improved outcomes. Also, minimally invasive pancreatoduodenectomy (MIPD) is increasingly becoming part of clinical practice for selected patients worldwide, as an alternative to open pancreatoduodenectomy (OPD) [1–3]. However, despite promising results from expertise centers, the implementation of minimally invasive techniques for PD is rather slow. This is probably caused by the conflicting outcomes on MIPD as reported by four randomized controlled trials (RCT) on laparoscopic MIPD (L-MIPD) [4–7]. Two single-center and one multicenter RCT showed benefits of L-MIPD in term of less intraoperative blood loss and reduction in length of hospital stay, as compared to OPD, with comparable postoperative morbidity and mortality [4, 5, 7]. However, the preliminary termination of the multicenter LEOPARD-2 trial, comparing L-MIPD and OPD, raised concern on the safety of MIPD due to a higher mortality rate after L-MIPD, diminishing the further implementation of L-MIPD [6]. Since then, the safety of MIPD remains a topic of debate.

Recently, the robotic platform has gained an important place in the surgical field [8]. Especially for pancreatic surgery, robotic surgery has become more popular due to the potential advantages over conventional laparoscopic surgery, including enhanced instrument mobility, 3D visualization, and improved ergonomics [9]. Although promising results on robotic PD (R-MIPD) from high volume expert centers have been reported, no level 1 evidence is available yet, and therefore, the role of R-MIPD is limited to retrospective data from single high-volume centers [10–13].

As MIPD is increasingly being implemented in clinical practice worldwide, a randomized controlled trial (RCT) comparing MIPD to OPD in high-volume centers that have completed the learning curve is needed to demonstrate that MIPD offers improved outcomes that justify the high costs, longer operative times, and learning curve. Furthermore, due to the ongoing uncertainty of the safety and additional benefits of MIPD, many patients affected by pancreatic or peri-ampullary neoplasms might not receive MIPD and do not benefit from potential advantages of an enhanced recovery, such as a reduction of the impact of complications or increased use and completion of adjuvant chemotherapy, compared with OPD.

Therefore, the DIPLOMA-2 trial is designed to primarily investigate the safety of MIPD in terms of morbidity and mortality, and additionally to assess if MIPD is superior to OPD in terms of time to functional recovery, in patients with pancreatic or peri-ampullary neoplasm. Moreover, the DIPLOMA-2 trial aims to compare surgical and oncological outcome, quality of life, and costs after MIPD and OPD. The results of the DIPLOMA-2 trial will answer the present uncertainties regarding safety and guide the further implementation of MIPD worldwide [14].

## Methods

### Design

The DIPLOMA-2 trial is an investigator-initiated, international, randomized controlled patient-blinded non-inferiority trial comparing MIPD versus OPD in patients with a neoplasm located in the pancreatic head or peri-ampullary region. Patients are randomly allocated to MIPD or OPD in a 2:1 ratio, respectively. This unequal randomization provides more statistical power for detecting adverse events in the MIPD group, and secondly will allow for maintenance of a higher annual MIPD volume of the participating surgeons, as MIPD outcomes are strongly associated with hospital volume [15].

Inclusion started after approval of the primary medical ethical review committee board (January 2022). Additionally, local ethical approval was gained for every participating center, before the local initiation of the study. All patients provide a written informed consent before randomization. This protocol was developed according to the SPIRIT guidelines [16].

### Study population

Adult patients with an indication for elective pancreatoduodenectomy because of a proven or suspected neoplasm in the pancreatic head or peri-ampullary region are assessed for eligibility in the DIPLOMA-2 trial. Patient are eligible to participate in case of upfront resectable pre-malignant or malignant disease.

### Inclusion criteria

In order to be eligible to participate in this study, a patient must meet all of the following criteria:Age of at least 18 years;Indication for elective pancreatoduodenectomy for a proven or suspected* premalignant or malignant neoplasm located in the pancreatic head, distal bile duct, duodenum, or ampulla of Vater;Upfront resectable disease (without induction/down-sizing radiotherapy and/or chemotherapy), with pre-operative multiphase CT scan showing no signs of vascular involvement^#^;Both MIPD and OPD are considered technically feasible for radical resection, according to the local treatment team;The patient is fit to undergo MIPD and OPD according to the operating team;Written informed consent given by the patient.

* Pathological proof is not mandatory as it is not common practice in some indications, and the decision for minimally invasive or open surgery after the trial will therefore also depend on the “suspected” diagnosis.

^#^ Neoadjuvant radiotherapy and chemotherapy are allowed in the study, only in case of an upfront resectable tumor. Induction treatment for an initially non-resectable tumor (i.e., locally advanced) is not allowed.

### Exclusion criteria

Patients meeting any of the following criteria will be excluded from participation in this study:Second malignancy necessitating resection during the same procedure;Chronic pancreatitis as indication or in medical history (according to the M-ANNHEIM criteria [17]);Any major vascular tumor involvement (portal vein, superior mesenteric vein, superior mesenteric artery, coeliac artery or hepatic artery) or distant metastases (M1) including involved distant lymph nodes on a CT scan maximum 28 days old;Body mass index ≥ 35 kg/m^2^;Pregnancy;Participation in another study with interference of the primary outcome (CCI®) or time to functional recovery.

### Randomization

Patient recruitment and the collection of written informed consent are performed at the outpatient clinic. Hereafter, all patients will be randomized centrally by the study coordinators using an online computer controlled permuted-block randomization module (Castor EDC, CIWIT B.V., Amsterdam, the Netherlands). Randomization between MIPD and OPD will be performed in a 2:1 ratio, with block sizes varying between 3, 6, and 9 patients. The entire randomization process will be concealed to all involved investigators, except the study coordinator. Randomization will be stratified for the minimally invasive technique (laparoscopic or robotic), the pre-operative risk of post-operative pancreatic fistula (normal versus high risk, based on BMI (< 25 kg/m^2^ and ≥ 25 kg/m^2^) and pancreatic duct diameter (< 3 mm or ≥ 3 mm) on pre-operative imaging), and for the indication (pancreatic ductal adenocarcinoma (PDAC) or other indication). Patients will be coded by a numeric randomization code, and the study coordinator will be the only one with access to it. The source data will be stored digitally and will be kept by the project leader for 15 years after the last patient’s follow-up is completed.

### Surgical technique and postoperative regime

Because of the pragmatic design of the DIPLOMA-2 trial, no specific standards for MIPD and OPD are provided. All procedure details will be recorded within an online case record form immediately after surgery. There are no restrictions regarding postoperative care, blood tests, drain management, the use of medication, or other kinds of co-intervention. However, the participating centers should provide the same postoperative care for both study arms, based on enhanced recovery principles, which include early mobilization and expanding oral intake as desired by the patient. The treating team will be asked to specify the use of this kind of additional (surgical) proceedings and medication in the online case record forms.

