### Statistical aspects

#### Sample size calculation

The DIPLOMA-2 trial is designed as a non-inferiority trial, hypothesizing that the mean CCI® score of MIPD is non-inferior to OPD. Calculations are based on results of the pan-European E-MIPS retrospective cohort study and on individual patient-data collected from the previous conducted RCTs on MIPD versus OPD. The sample size is calculated using PASS 2022 software to achieve 80% power (1-β) in a per-protocol analysis with the following assumptions: 2.5% one-sided significance level (α), expected difference of the mean CCI® score in the MIPD and OPD group of 0 points, and a non-inferiority margin of 7.5 points, standard deviation of 20 points in both groups, including 5% metastasized disease, a 10% conversion rate and a 3% lost-to-follow-up rate after randomization leads to a total number of patients to be randomized of 288 (192 in the MIPD study arm and 96 in the OPD study arm). For time to functional recovery, we assume MIPD will result in a reduction of 2 days (7 days in the MIPD group versus 9 days in the OPD group. Time to functional recovery will be measured in days and will be tested for superiority using the Wilcoxon (Gehan-Breslow) test or the log-rank test (based on non-normal distribution). With a one-sided testing, assuming 5% metastatic disease, 10% conversion rate, and 3% loss to follow-up, a sample of 247 patients (159 in the MIPD group and 88 in the OPD group) in a per protocol analysis achieves 80% power to detect a 28% reduction of time to functional recovery (i.e., 6.5 days in the MIPD group; hazard ratio = 0.72). The estimated median time to functional recovery of 9 days in the OPD group is based on results of the LEOPARD-2 trial and corresponds to a median TTFR reduction of 2.5 days.

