The primary outcome measure “CCI®” will be expressed as means (standard deviations) or medians (interquartile ranges) and will be tested for non-inferiority using independent samples *t*-test or Mann–Whitney *U* test, as appropriate dependent of the distribution. The most important secondary outcome measure “time to functional recovery” will be measured in days and will be tested for superiority using the Wilcoxon (Gehan-Breslow) test or log-rank test, depending on the distribution. Secondary analysis will include correction for censored patients (death before time to functional recovery obtained). For the primary study outcome, the lower limit of the two-sided 95% confidence interval of the difference in proportions will be reported and compared with the non-inferiority margin. Additionally, the individual functional recovery criteria will be analyzed separately. Major complications, expressed in proportions, will be tested for non-inferiority using chi-square or Fisher’s exact test as appropriate. The distribution of variables will be determined using several plots (boxplot, Q-Q plot and histogram) and the Kolmogorov–Smirnov and Shapiro–Wilk tests. For comparison of normally distributed continuous variables, the independent samples *t*-test will be used, and values will be expressed as means (standard deviations). Continuous non-normally distributed variables will be compared using the Mann–Whitney *U* test, and values will be expressed as medians (interquartile ranges). Categorical variables will be compared by chi-square or Fisher’s exact test as appropriate, and values will be expressed as proportions. A two-tailed *p*-value < 0.05 will be considered statistically significant. Time to event endpoints, such as survival, will be calculated using Kaplan–Meier estimations. A Cox regression analysis will be performed to investigate predictors of postoperative survival. All parameters with a *p*-value < 0.1 in a univariable analysis will be included in the multivariable Cox regression analysis. Additionally, multivariable analyses will be performed to determine predictors for primary and secondary study outcomes, for example the occurrence of major complications, postoperative pancreatic fistula, and R0 resection. Furthermore, predictors for receiving adjuvant chemotherapy or readmission will be assessed.

For subjects who are lost to follow-up, a sensitivity analysis will be performed to determine best case/worst case scenarios.

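### The pooled two-sample test of CCI leaves between-centre variation in the error term and costs a little precision; a random centre intercept recovers it at negligible cost

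*Protocol article*

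**What the plan says.** All references are to the protocol article.

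- **Surgical technique and postoperative regime:** "There are no restrictions regarding postoperative care, blood tests, drain management, the use of medication, or other kinds of co-intervention". The one constraint is that "the participating centers should provide the same postoperative care for both study arms", within an enhanced-recovery framework that names early mobilisation and oral intake.
- **Randomization:** "Randomization will be stratified for the minimally invasive technique (laparoscopic or robotic), the pre-operative risk of post-operative pancreatic fistula"; the third factor is indication (PDAC or other). Centre is not listed.
- **Quality and safety:** each centre takes part with one technique only, laparoscopic or robotic.
- **Design:** the 2:1 ratio is justified partly by the dependence of MIPD results on hospital volume.
- **Statistical analysis:** CCI is compared by an independent-samples t-test or a Mann–Whitney test. Time to functional recovery "will be tested for superiority using the Wilcoxon (Gehan-Breslow) test or log-rank test, depending on the distribution". Neither test is given a centre term. Centre enters only through a planned subgroup analysis by annual MIPD volume, and a detailed SAP is to follow before database lock.

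**The concern.** The protocol gives its own reasons to expect centres to differ: local care is unrestricted, and volume is said to matter. Analgesia, intravenous fluids and CRP are also components of the functional-recovery definition. The technique stratum balances the arms between the laparoscopic and the robotic group of centres, but not between centres within a group. Each centre's MIPD share therefore varies by chance, and the pooled test counts differences between centres as noise. What is at stake is the width of the confidence interval that is compared with the 7.5-point margin. The named tests are a stated choice, so this is more than silence on a detail.

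**Working it through.** **Inputs.** From Sample size calculation: one-sided α of 2.5%; "to achieve 80% power (1-β) in a per-protocol analysis"; "expected difference of the mean CCI® score in the MIPD and OPD group of 0 points"; "a non-inferiority margin of 7.5 points, standard deviation of 20 points in both groups"; 288 randomised (192 MIPD, 96 OPD); losses of 5% (metastases), 10% (conversion) and 3% (follow-up). From the Abstract: 14 centres. Assumed, because the documents give no value: between-centre ICC for CCI of 0 to 0.20, and a centre SD of 0 to 0.4 on the log scale for recovery time. The SD of 20 is taken to include between-centre variation.

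**1. The plan's own figure.** With conversion applied to MIPD only, 192 × 0.95 × 0.90 × 0.97 = 159 and 96 × 0.95 × 0.97 = 88. These are the 159 and 88 that the protocol gives for recovery.

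- Evaluable set: SE = 20 × √(1/159 + 1/88) = 2.66; power = Φ(7.5/2.66 − 1.96) = 80.6%. The planned 80% is reproduced.
- All 288: SE = 20 × √(1/192 + 1/96) = 20 × 0.125 = 2.5; power = Φ(3 − 1.96) = 85.1%.

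**2. Size of the centre-mix component.** Its SD is roughly 0.125 × 20 × √ICC = 2.5 × √ICC.

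- ICC 0.05: 0.56, a 95% range of about ±1.1 points.
- ICC 0.10: 0.79, about ±1.5 points.

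A simulation used 288 patients, 14 unequal centres (half assumed laparoscopic, half robotic), 2:1 blocks of 3/6/9 in 8 strata, normal outcomes and 4,000 runs per setting. It gave slightly smaller SDs of 0.50 and 0.71. The mean was within 0.02 points of zero at every ICC.

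The right comparator is total chance error, 1.96 × 2.5 = ±4.9 points. By the formula, centre mix is 0.56²/2.5² = 5% of that variance at ICC 0.05 and 10% at ICC 0.10. Removing all of it at ICC 0.05 would narrow the half-width from 4.9 to 4.9 × √0.95 = 4.8.

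**3. Type I error.** At a true difference of 7.5 points, the pooled t-test declared non-inferiority in 2.0–3.0% of runs (nominal 2.5%, Monte Carlo SE about 0.25 points), with no upward trend as ICC rose. A second 4,000-run simulation gave 2.1–2.7%.

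**4. Gain from modelling centre (CCI, N = 288).** The two adjusted analyses come from separate simulations, so each is compared with its own pooled test.

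| ICC | Centre as fixed terms: power, pooled → adjusted | Random centre intercept (REML): change in power |
|---|---|---|
| 0 | 85.4% → 83.8% | none (83.8% vs 84.0%) |
| 0.05 | 85.1% → 85.4% | about +1 point |
| 0.10 | 85.2% → 87.3% | about +2 points |
| 0.20 | 85.9% → 90.4% | about +5 points |

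Fixed centre terms cost 1.6 points when centres are alike; the random intercept does not. In standard-error terms the pooled analysis is about 1–2% less precise at ICC 0.05 and 2–3% at 0.10. Complete removal would give at most 1/√0.95 = 1.026 and 1/√0.90 = 1.054; the realised gain is smaller because centre effects have to be estimated.

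**5. Time to functional recovery.** The protocol says only that testing is one-sided. With 247 events, √(247 × 0.644 × 0.356) × |ln 0.72| = 2.47. Power is then Φ(2.47 − 1.645) = 80% at one-sided 5% and Φ(2.47 − 1.96) = 70% at 2.5%, so 5% reproduces the stated power and was used. Data were exponential with medians of 9 and 6.5 days, arms of 159 and 88, and 600 runs per setting (Monte Carlo SE about √(0.75 × 0.25/600) = 1.8 points).

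| Centre SD (log scale) | Log-rank | Cox, random centre effect | Difference (points) |
|---|---|---|---|
| 0 | 78.0% | 75.8% | −2.2 |
| 0.2 | 75.5% | 74.8% | −0.7 |
| 0.3 | 73.8% | 75.8% | +2.0 |
| 0.4 | 71.2% | 75.3% | +4.1 |

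A log-rank test stratified by 14 centres did worse: 68–72%, against 78% unstratified at SD 0 and 71% at SD 0.4.

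**The case against.** The strongest reply is that individual randomisation makes centre mix a matter of chance, as with any unstratified prognostic factor, and that a planning SD drawn from a pan-European cohort and pooled trial data probably already contains it. That stands. A reader might infer from the local-care clause that the MIPD–OPD contrast is biased, or that ±1.1 to ±1.5 points against a 7.5-point margin threatens the non-inferiority conclusion. The documents support neither: the component averages zero, is already part of the ±4.9 points of chance error, and leaves type I error at its nominal level.

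It is also said that the benefit has no established sign. That holds for fixed centre terms and for the recovery model, but not for a random intercept on CCI, which lost nothing at ICC 0.

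Three further replies have some weight.

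- Enhanced-recovery principles, centre and surgeon volume thresholds, and the technique stratum all narrow or partly balance centre differences.
- The volume statement concerns MIPD results, which suggests a treatment effect that varies by centre. A random intercept does not address that.
- The SAP, not shown, may already model centre. Its absence from the article is therefore no omission; the point rests on the pooled tests that the article does name.

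**Conclusion.** This is a minor point of precision. The pooled CCI test is valid but slightly inefficient: its standard error is about 1–2% too large at ICC 0.05 and 2–3% at 0.10, worth about 1 and 2 points of power, and about 5 points at ICC 0.20. If centres are alike there is nothing to gain and nothing to lose. The sample size of 288 is unaffected.

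The figures rest on assumed ICCs, normally distributed outcomes, all 288 patients analysed as randomised, and a total SD of 20 that includes centre variation. A reader might also infer that the recovery test should be replaced by a random-effect Cox model. The calculations do not support that: the change runs from about −2 to +4 points depending on an unknown variance, with simulation error of about 1.8 points per estimate, and was examined only under proportional hazards.

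**What to change.** State in the SAP, before database lock, that the difference in mean CCI and its two-sided 95% CI come from a linear model with treatment as a fixed effect and centre as a random intercept (REML), and that this interval is compared with the 7.5-point margin. If the centre variance is estimated as zero, the model reduces to the pooled comparison.

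For time to functional recovery, keep the stated test as primary and add a Cox model with a random centre effect as a sensitivity analysis, noting its proportional-hazards assumption and that its hazard ratio is conditional on centre. Do not stratify the log-rank test by 14 centres: 247/14 is about 18 patients per centre, and power falls when centres are similar.

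The cost is SAP wording only. Centre is already recorded, and sample size, randomisation and data collection do not change.
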